**Methods/design:**

This is a multicenter, multi-informant and multi-method randomized clinical trial study with a 2 by 2 factorial experimental design. Participants (*N* = 100) are children (4–12 years), and their parents, who have been exposed to interparental violence. The main aim of the study is to test the effects of two parental components as an addition to a trauma focused cognitive behavioral based group therapy for reducing children’s symptoms. Primary outcome measures are posttraumatic stress symptoms, and internalizing and externalizing problems in children. The secondary aim of the study is to test the effect of the two added components on adjustment problems in children and to test whether enhanced effects can be explained by changes in children’s responses towards experienced violence, in parental availability, and in quality of parent-child interaction. To address this secondary aim, the main parameters are observational and questionnaire measures of parental availability, parent-child relationship variables, children’s adjustment problems and children’s responses to interparental violence. Data are collected three times: before and after the program and six months later. Both intention-to-treat and completer analyses will be done.

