### Statistical analyses and sample size calculation

All variables are measured on at least an ordinal scale. All scale scores will be examined for normality. Should we observe deviations, steps will be taken to ensure optimal estimation of parameters in our analyses. The proposed study includes a nested structure, because individuals are treated within groups. Following the recommendations by Peugh [118], we will calculate design effects to assess group-level dependency and examine whether multi-level modeling is required. To ensure comparability of the randomized conditions, we will control for duration and severity of the IPV [45], parental psychopathology [46], and new incidents of IPV. Power calculations were performed using the program G*power 3 [119], assuming that individual-level effects can be treated as independent data. We determine required sample size to be 100 parent-child dyads, achieving statistical power of at least .80 for the primary and secondary objectives, as described in more detail in the following paragraphs. We will test for the randomness of missing data. If this is the case we will use multiple imputation.

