### Primary objective

The first goal of the present study is to examine the efficacy of two parental components that complement a TF-CBT-based core treatment for children who have been exposed to IPV. Therefore, a multiple regression analysis will be executed with two dummy variables as independent variables, representing both parental components (dummy 1 = parent preparatory program present vs. absent; dummy 2 = parent-child interaction sessions present vs. absent) and their interaction. Dependent variables are child symptoms (primary outcomes) at the three time points (T1, T2, and T3) clustered into 1) Trauma symptoms, 2) Internalizing symptoms, 3) Externalizing symptoms. Analyses will be independently executed for the three dependent variables. Because children in each group receive intervention, a medium effect size is expected (f^2^ = .15). With a maximum of five predictors and an alpha of .05, we achieve a power of .84 with 100 children included in the study.

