### Secondary objectives

To investigate associated changes between: child symptoms, on the one hand, and 1) child responses (i.e., child emotional, behavioral, and cognitive responses), 2) parental availability and 3) parent-child interaction on the other, we will use the stepwise procedure in multivariate regression analyses with a maximum of 4 tested predictors. With a sample size of 100, alpha of .05 and medium effect size (f^2^ = .15), we will achieve a power of .87 in analyses with 4 individual predictors. We will use latent variables for child responses, parental availability and parent-child interaction.

We will also use multivariate regression analyses to study the fourth goal, namely which mechanisms explain how the two components added to the TF-CBT-based Horizon treatment contribute to the effectiveness of TF-CBT-based Horizon treatment. We will follow Holmbeck’s recommendations [120] for these mediational analyses and will test the robustness of our results by using the bootstrapping method. These analyses will allow us to determine whether the parent-child interaction variables and parental availability partly or fully mediate the effects of each parental component on child symptoms. Specifically, we will test whether, as predicted, the preparatory program leads to increased parental availability and whether the parent-child interaction sessions lead to improved parenting behavior. Also, we will explore whether these changes lead to a reduction in symptoms. Because at least partial mediation is assumed, a small to medium effect size is chosen (f^2^ = .10). Two models are tested. A first model with component 1 (preparatory parent program) and parent availability as independent variables. And a second model with component 2 (parent-child interaction sessions) and parent-child interaction as independent variables. With a sample size of 100, alpha of .05 and medium effect size (f^2^ = .10), we will achieve a power of .80 if 2 predictors are tested in the regression.

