### Ethical considerations

The study protocol has been approved by the Medical Ethics Committee of the VU University Medical Center in Amsterdam, the Netherlands (METC VUmc 2011/101/NL39277.029.12). All substantial amendments will be presented to the METC and to the competent authority. Non-substantial amendments will not be notified to the accredited METC and the competent authority, but will be recorded and filed by the sponsor, ZonMw, the Dutch organization for healthcare research and innovative care. All changes will be described and discussed in the publications of the study results.

The HORIZON has been used to treat children who have experienced IPV for more than 10 years in several children and youth treatment centers in the Netherlands and does not seem to involve risks for participants. Nevertheless, should a child or a parent seem adversely affected by therapy, questionnaires or observational tasks as observed by the researchers or therapists, it may be decided to (temporarily) discontinue participation in this study. Participants can leave the study at any time for any reason if they wish to do so without any consequences. Withdrawal of participants from the study will have no impact on their treatment. Participants who withdraw from the study will not be replaced, because there is no place for them in the therapy groups, and it is not possible for parents and children to start at a later time during treatment. Should participants withdraw from the treatment, these parents and children will be followed according to the intention to treat principle. They will be asked fill in the questionnaires and the observational tasks.

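### Multiple imputation is made conditional on a test that cannot show the data are missing at random, so it can be withheld when it is needed

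*Protocol article*

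**What the plan says.** The rule closes the opening paragraph of the section Statistical analyses and sample size calculation: "We will test for the randomness of missing data. If this is the case we will use multiple imputation". The article does not name the test, does not say which meaning of random is intended, and gives no method for the case where the test finds otherwise.

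Two other places bear on it. The Abstract (Methods/design) states "Both intention-to-treat and completer analyses will be done". Under Ethical considerations, families who stop treatment are to be "followed according to the intention to treat principle", while families who leave the study are not replaced. The sample size is 100 dyads, with no allowance for dropout stated.

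The Primary objective section of the analysis plan regresses child symptoms on two component indicators and their interaction. Symptoms at T1 are listed among the dependent variables. The named control variables are duration and severity of the violence, parental psychopathology and new incidents. T1 symptoms are not named as a covariate.

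**The concern.** The rule fails on either meaning of random.

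- **Missing completely at random.** This can be tested, but the condition then points the wrong way for bias. If it holds, complete cases are unbiased and imputation only recovers precision. If the test rejects, missingness may depend on observed scores, and that is the situation in which imputation helps.
- **Missing at random.** Observed data cannot distinguish this from missing not at random, so the condition cannot be checked and the rule cannot be carried out.

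The estimate exposed is the intention-to-treat effect of each component. Missing outcomes are foreseeable. T1 falls 7 weeks before the core treatment, which has 15 weekly sessions, and T3 comes 6 months (about 26 weeks) later: 7 + 15 + 26 = 48 weeks. If imputation is withheld and available cases are used, the intention-to-treat and completer analyses move towards each other just when dropout looks selective.

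**Working it through.** **1. The plan's own figures.** The missing-data rule carries no number. The nearest stated figure is the primary power: "With a maximum of five predictors and an alpha of .05, we achieve a power of .84 with 100 children included in the study". Overall F test, f² = .15, 5 predictors, N = 100: λ = f² × N = .15 × 100 = 15, with df 5 and 100 − 5 − 1 = 94. Power is .843, which reproduces .84. The two secondary figures also reproduce: .874 against .87 (4 predictors, f² = .15) and .803 against .80 (2 predictors, f² = .10). All three need 100 complete outcomes. With 80 analysed, the primary power is .732. Imputation would recover only part of that loss, so it is not charged to the rule.

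**2. Bias when imputation is withheld.** Assumptions, none from the documents:
- 20% missing in one arm, with logistic dropout on the standardised T1 score X;
- T1-outcome correlation ρ = .6;
- no T1 adjustment;
- two arms of 50, children treated as independent, true effect zero.

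With p(X) the dropout probability, the available-case mean in that arm shifts by ρ × E[X(1 − p(X))] / E[1 − p(X)].

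**3. How often the rule withholds imputation, and the average result.** The test is a t-test of T1 in missing against observed children at the 5% level. If it rejects, available cases are used. If not, outcomes are imputed from T1 and component, using the fitted mean, which suffices for bias. There were 20,000 simulated trials per setting. The paired figures are for the other arm missing 20% completely at random / missing none.

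| Odds ratio per SD | Shift if withheld (SD) | Test rejects | Average bias under the rule (SD) |
|---|---|---|---|
| 1.65 | −.057 | 16% / 25% | −.012 / −.030 |
| 2.01 | −.077 | 26% / 41% | −.021 / −.046 |
| 2.72 | −.103 | 41% / 65% | −.044 / −.083 |

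Imputing in every trial gave an average bias within .003 SD of zero in all six settings. The sampling SD of the available-case contrast is about .21 to .22.

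The average under the rule is roughly rejection rate × shift, for example .41 × .103 = .042. It is larger when the other arm is complete, because trials that pass the test are then a selected set with some baseline imbalance.

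**4. Does adjusting for T1 remove the problem?** A second simulation (N = 100 in four cells, 2,000 replicates, true component effect assumed −0.50 SD) adjusted for T1. It used a two-variable test of missing completely at random on T1 and T2, with T3 missing in 15% or 25%.

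| Dropout depends on | Test rejects | Complete cases, mean | Imputation using T1 and T2, mean |
|---|---|---|---|
| nothing | 4% to 5% | −0.50 to −0.51 | −0.50 to −0.51 |
| T1 only (in the model) | 31% to 94% | −0.50 to −0.51 | −0.50 to −0.51 |
| T2, differently by condition | 4% to 68% | −0.54 to −0.64 | about −0.50 |
| T3 itself (not at random) | 23% to 33% | −0.66 to −0.74 | −0.63 to −0.70 |

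The test rejects most often where complete cases are sound (row 2). It can stay at its nominal rate where they are biased (row 3, opposite dependence in the two conditions). Its result is a poor guide to whether imputation is needed.

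**The case against.** Four points can be made for the plan.

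1. **Selective dropout need not bias complete cases.** A reader might infer that the rule withholds imputation exactly when complete cases are biased. That is too strong. If dropout depends only on variables in the model, complete cases stay unbiased although the test rejects, and the planned controls cover some likely drivers of dropout. This stands. It does not rescue the rule, because T1 symptoms are not named as a covariate and bias remains with T1 adjusted when dropout follows T2 differently by condition.

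2. **The fallback is not stated.** A reader might take the article to prescribe complete-case analysis. It does not. That is inferred from the absence of any alternative and from the planned completer analysis. A full protocol or analysis plan may give another method. The flaw is in the condition that the article does state.

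3. **The weak test partly offsets the harm.** A reader might add the test's low power to the full .06 to .10 SD. The documents give no ground for that. When the test fails to reject, imputation goes ahead, so low power lowers the average bias. What low power does is make the choice of method largely a matter of chance.

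4. **Imputation is no cure for dropout that is not at random.** True: it was also biased in that case. Continued assessment of families who stop treatment will also reduce missing outcomes. Neither point supports using this test as a condition.

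**Conclusion.** The rule is wrong as written and should be changed. It rests on a test that can address only missing completely at random, and it can withhold imputation when the intention-to-treat contrast needs it.

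The size is modest. Under the stated assumptions the contrast is off by about .06 to .10 SD in trials where imputation is withheld, which is less than half its sampling SD. That occurs in roughly 16% to 65% of trials, so the average bias is about .01 to .08 SD. The missingness rate, correlation, odds ratios and one-arm pattern are not in the documents, and the simulations ignore clustering by treatment group. The logical fault in the rule depends on none of these numbers; the inferred fallback matters only for the bias figures. The documents do not support a claim that the primary result will be materially wrong.

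**What to change.** Delete the test as a condition. State that the intention-to-treat analysis is always run under missing at random, by multiple imputation or a likelihood-based mixed model, using T1 scores, the two component indicators and the treatment group as a cluster level. The test may be kept as description, provided nothing depends on it. Keep the completer analysis as supportive. A sensitivity analysis for dropout that is not at random is desirable but optional.

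The cost is a change of wording and modest programming. The T1 scores are already collected, and sample size and assessments do not change.

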### Primary objective

The first goal of the present study is to examine the efficacy of two parental components that complement a TF-CBT-based core treatment for children who have been exposed to IPV. Therefore, a multiple regression analysis will be executed with two dummy variables as independent variables, representing both parental components (dummy 1 = parent preparatory program present vs. absent; dummy 2 = parent-child interaction sessions present vs. absent) and their interaction. Dependent variables are child symptoms (primary outcomes) at the three time points (T1, T2, and T3) clustered into 1) Trauma symptoms, 2) Internalizing symptoms, 3) Externalizing symptoms. Analyses will be independently executed for the three dependent variables. Because children in each group receive intervention, a medium effect size is expected (f^2^ = .15). With a maximum of five predictors and an alpha of .05, we achieve a power of .84 with 100 children included in the study.

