### Trial objectives

In the present project, we will examine the efficacy of the two parental components of the HORIZON, the preparatory program for parents and the parent-child interaction sessions. HORIZON is a TF-CBT-based group treatment for children exposed to IPV. For a complete description of the treatment in Dutch see [10, 44], and for a summary see paragraph ‘Intervention’. In a randomized-controlled design, we will add the parental components to a TF-CBT-based core treatment to examine their independent and combined effects on parents’ and children’s outcomes. Overall, we expect both parental components to add to the efficacy of the TF-CBT-based core treatment. Specifically, we expect that, as compared to parents who did not participate in the preparatory program, parents who participated in the preparatory program show a greater increase in parental availability. In the same vein, we expect that the parents who participated in the parent-child interaction sessions show a greater increase in effective and positive parenting and a greater decrease in negative parenting than parents who did not participate in these sessions. These effects of the parental components should contribute to parents’ and children’s outcomes and reduction of symptoms.

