### Primary objectives

The primary objective of the present study is to examine the efficacy of two parental components that complement a TF-CBT-based core treatment for children who have been exposed to IPV. Specifically, the study involves a randomized controlled trial with a 2 (parent preparatory program present vs. absent) X 2 (parent-child interaction sessions present vs. absent) factorial design to evaluate the effects of these two parental treatment components on child symptoms.

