*The Children’s Responses to Trauma Inventory Revised version* [90] is a self-report measure for children aged 8–18 years and consists of 34 items. Children answer, on a 5-point Likert scale, to which extent a reaction to a traumatic event was present during the past week. The instrument has 4 subscales: intrusion, avoidance, arousal, and other child-specific responses (e.g., feelings of guilt, regressive behavior, reckless behavior, fear of the dark, fear of going to the toilet at night, separation anxiety, sadness, crying, feeling tired, and psychosomatic complaints). A recent study found good psychometric properties for the scale, with Cronbach’s α of 0.92 for the total scale, and α ranging from 0.72 to 0.81 for the four subscales [91]. The parent-reported questionnaire is intended for parents of children age 4 to 18 years. The scale consists of the same 34 items measuring intrusion, avoidance, arousal, and nonspecific symptoms during the last week. Previous research shows sufficient reliability (α total scale = 0.92) and good convergent and discriminant validity [92]. To assess concordance between parent- and child-reported trauma symptoms and parental insight in the child’s trauma symptoms, we will instruct parents to fill out the questionnaire how they think the child will answer and will compare child and parent forms. This information is obtained at session 1, 9 and 15.

*During the therapy*, in session 6, children will be asked to draw and talk about the most adverse incident they can remember about the IPV. This is part of the regular treatment protocol of the HORIZON for children. In addition, in session 6, we will ask the parents in the parallel group to write down what they think their child will talk about with respect to the most aversive IPV incident. The answers to this question from both parent and child will be compared. One of the aims of the preparatory program is to coach parents to differentiate between their own trauma-history and the one of the child. If this aim is achieved, we hypothesize that parents in treatment condition 1 & 2 (see Fig. 1) will more often provide an answer that is similar to their child’s to the above question than the parents in treatment condition 3 & 4 (see Fig. 1).

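### The primary model does not name the contrast that tests each parental component; read as 0/1 dummies plus their product, its coefficients are effects only where the other component is absent

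*Protocol article*

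**What the plan says.** All references are to the Protocol article.

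- **Design.** Under Primary objectives the trial is a "2 (parent preparatory program present vs. absent) X 2 (parent-child interaction sessions present vs. absent) factorial design", meant to evaluate what the two components do to child symptoms. Under Trial objectives the components are added to the core treatment "to examine their independent and combined effects on parents’ and children’s outcomes".
- **Primary model.** Under Primary objective, in the statistical section, the independent variables are two indicators with their product: "dummy 1 = parent preparatory program present vs. absent; dummy 2 = parent-child interaction sessions present vs. absent) and their interaction". The model is run separately for trauma, internalizing and externalizing symptoms. No numeric codes, no centring and no named contrast are given.
- **Power.** The same paragraph says "a medium effect size is expected (f^2^ = .15") and "With a maximum of five predictors and an alpha of .05, we achieve a power of .84 with 100 children included in the study".
- **Wording of component effects elsewhere.** Trial objectives expects that, "as compared to parents who did not participate in the preparatory program, parents who participated in the preparatory program show a greater increase" in availability. Parental availability, on the session 6 question, says "we hypothesize that parents in treatment condition 1 & 2 (see Fig. 1) will more often provide an answer that is similar" to the child's than parents in the other two conditions. Both compare everyone with the preparatory program with everyone without it.

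**The concern.** In a regression with 0/1 indicators and their product, the coefficient of the first indicator is not the effect of the preparatory program across the trial. It is the difference between preparatory program only and core treatment only. The second coefficient is likewise interaction sessions only against core treatment only. Children who received both components enter these two tests only through the residual variance.

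A factorial design is normally chosen so that every child contributes to the estimate of both components. If the two coefficients were reported as the component effects, that gain would not reach the results. With a true interaction, the reported figure would also be the effect in one half of the design, presented as the effect of the component. With no contrast fixed in advance, the choice between the simple and the averaged effect could also be made after seeing the data, and the two can differ in size and significance for each of three outcomes.

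**Working it through.** **1. The plan's own power figure.** Inputs from Primary objective: f² = 0.15, five predictors, alpha .05, N = 100. For the overall F test, the numerator df is 5, the denominator df is 100 - 5 - 1 = 94, and the noncentrality is f² × N = 0.15 × 100 = 15. The noncentral F distribution gives power 0.843, so the stated .84 reproduces. The same formula reproduces the two figures under Secondary objectives: 0.874 for four predictors (stated .87), and 0.803 for f² = .10 with two predictors (stated .80). A 1-df test at f² = .15 would have power 0.970. The .84 is therefore the joint test of all five predictors. That test is the same whichever way the two factors are coded.

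**2. What the coefficients mean.** Write the model as E(Y) = b0 + b1·A + b2·B + b3·A·B, with A and B coded 0/1 for the preparatory program and the interaction sessions.

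- Effect of A where B is absent: b1.
- Effect of A where B is present: b1 + b3.
- Effect of A averaged over B: b1 + b3/2.

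With codes -1/2 and +1/2, the coefficient of A is itself the averaged effect. The fitted values and the test of the product term are unchanged.

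**3. Precision.** Assumptions, not given in the document: 25 children in each of four cells (100/4), outcome SD 1, independent children, no covariates, no dropout.

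- SE of b1 = sqrt(1/25 + 1/25) = sqrt(0.08) = 0.283.
- SE of b1 + b3/2 = sqrt(1/50 + 1/50) = sqrt(0.04) = 0.200.
- Ratio = 0.283/0.200 = 1.41, so the variance is doubled.
- SE of b3 = sqrt(4/25) = 0.400 under either coding.

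**4. Power with additive effects.** Two-sided alpha .05, noncentral t with 100 - 4 = 96 df, noncentrality = effect/SE:

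| Effect of each component (SD) | 0/1 coefficient | Averaged effect |
|---|---|---|
| 0.4 | .29 | .51 |
| 0.5 | .42 | .70 |
| 0.6 | .56 | .84 |

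To link this to the plan's own effect size: if f² = .15 came wholly from two equal additive components, then f² = 2 × d²/4 = d²/2, so d = sqrt(0.30) = 0.55. Power per component is then .48 with the 0/1 coefficient and .77 with the averaged effect.

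**5. Power and estimate with an interaction.**

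- *Sub-additive:* 0.6 SD alone, 0.2 SD alongside the other component. The 0/1 coefficient estimates 0.6 with power .56. The averaged effect is (0.6 + 0.2)/2 = 0.4 with power .51. The 0/1 test is slightly the more powerful, but it estimates a different effect.
- *Super-additive:* 0.2 SD alone, 0.6 SD alongside the other. The 0/1 coefficient estimates 0.2 with power .11. The averaged effect is again 0.4 with power .51.

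**The case against.** The strongest reply is that the document commits no error here. It prints no numeric codes and never says that the raw coefficients are the tests of efficacy. The model is fitted to all 100 children, and b1 + b3/2 from that same fit has the full factorial precision. The only test that is powered does not depend on coding. Contrast coding is often left to the analysis plan, which is not shown.

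Much of this stands. A reader might infer that the model throws away half the sample, or that it cannot test the component effects. The text does not support either: the loss arises only if 0/1 coefficients are reported as the component effects. Nor is the power loss general, as the sub-additive case shows.

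A reader might also take the two participated-versus-not statements as proof that the primary hypotheses are marginal. They concern parental availability and parent-child agreement at session 6, not child symptoms. They show how the authors think of a component effect, but they do not fix the primary contrast. For child symptoms, the aim of adding to the core treatment is compatible with comparing one component plus core against core alone, and the product term serves the interest in combined effects.

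What does not stand is that nothing needs changing. The article does not leave the coding wholly open: it specifies dummies for present versus absent plus their product, and the default output of that model is the simple effect. The joint test cannot say which of two components works, and that is the primary question.

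**Conclusion.** The concern holds in conditional form. The plan names the terms of the primary model but not the contrast that tests each component. Under the usual 0/1 reading, the coefficients that software prints are effects in the absence of the other component, based on two of four cells. With 25 independent children per cell, the standard error is 1.41 times that of the averaged effect, and power at an additive 0.5 SD is .42 rather than .70. With an interaction, the power difference can vanish or widen, and the coefficient no longer estimates the average.

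The absolute powers are illustrative. Whole treatment groups of about eight families are allocated by lottery, so equal cells are not assured, and dependence within groups would lower all these powers; the direction of the coding comparison would stay the same. The stated .84 is arithmetically correct for the joint test, but it is not the power to detect either component's effect.

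**What to change.** In the Primary objective paragraph of the statistical section:

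1. Code both factors -1/2 and +1/2, or keep 0/1 codes and specify the averaged contrasts b1 + b3/2 and b2 + b3/2.
2. Name these two 1-df effects as the primary component tests for each outcome, and give power for them beside the joint test.
3. Keep the product term as the test of non-additivity.
4. Report the simple effects with confidence intervals as supporting results.

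The cost is a sentence or two of analysis wording; no data, visits or participants are added, and model fit and the interaction test do not change. One small downside: if there is a true interaction, the averaged effect must be interpreted alongside the simple effects. If the authors do want component plus core against core alone as the primary comparison, they should say so and base the power on that two-cell contrast.
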